## Definitions

**Parasite clearance:** at least two consecutive negative smears for parasites obtained within an interval of 8 to 24 hours, post-dosing.

**Fever clearance:** at least two consecutive normal body temperature measurements obtained within an interval of 8 to 24 hours, post-dosing.

**Treatment failure:** the definition of treatment failure includes the following:

- ◆ Clinical deterioration due to *P. vivax* illness requiring hospitalization in presence of parasitaemia.
- ◆ Presence of parasitemia and axillary temperature  $\geq 37.5^{\circ}\text{C}$  any time between Day 3 and Day 28.
- ◆ Presence of parasitemia on any day between Day 7 and Day 28 irrespective of clinical condition.

**Cure on Day 14:** no parasitaemia on Day 14 irrespective of axillary temperature without previously meeting any of the criteria of treatment failure.

**Cure on Day 28:** no parasitaemia on Day 28 irrespective of axillary temperature without previously meeting any of the criteria of treatment failure.

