#### **4.11. Rescue Medication**

Treatment failures will be treated with the best antimalarial therapy available in the country where the study is conducted. All procedures to be performed at Day 28, including sampling for PCR, preparation of a thin and thick films and **whole blood sample for measurement of pyronaridine and/or chloroquine/chloroquine metabolites blood levels** must be undertaken before rescue medication is administered.

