|                                            | 
 
➤ Blood biochemistry and urinalysis
 
➤ Thick blood films (2) prepared 8-hourly
 
➤ Adverse events recording
 
➤ Concomitant medication recording
 
➤ Patient scheduled for follow up visits on Days 7, 14, 21, 28, 35 and 42
 
➤ Patient may be discharged from study site if parasite- and fever-free, with instructions to return in case of any recurrence of symptoms
 
 
note: If parasites and fever have not cleared on Day 3, the patient should be followed up until total clearance of parasites. If parasitaemia remains significant, the patient should be viewed as a treatment failure and withdrawn from the study. All End of Study Assessments (Day 28) should be performed before discharge and before rescue medication is given.
 
 
➤ Patient provided with an appropriate bed net
 
 |
| Assessment D7
(+/- 1 day)       | 
 
➤ Vital signs: BP and HR
 
➤ Temperature recorded
 
➤ Clinical signs and symptoms of malaria (if clinically indicated)
 
➤ 12-lead ECG (if clinically indicated)
 
➤ Haematology
 
➤ Blood biochemistry and urinalysis
 
➤ Thick blood films (2) for asexual parasites and gametocytes counts (the total count is recorded)
 
➤ Thin blood film (as a reserve)
 
➤ Sample for PCR (as a reserve)
 
➤ Adverse events recording
 
➤ Concomitant medication recording
 
                                                                                                                                                                                                                                                                                                                                                     |

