#### Efficacy Evaluable (EE) Population

The efficacy evaluable (EE) population will include those patients in the ITT population meeting pre-defined criteria as follows:

1. Having completed a full course of study medication and having known efficacy endpoints.
2. No missed dose due to vomiting, as recorded on the 'study medication administration page' of the CRF, except at Day 0 where a patient may vomit after the first drug administration and have a repeat full dose. In this case, the repeated dose should not be vomited.

3. No concomitant medication (except paracetamol) which may interfere with the treatment outcome, up to Day 14. The list of forbidden medication is given in Attachment 5. A medical review will be performed to confirm the exclusion of a patient from the EE population.
  4. No concomitant disease, such as Tuberculosis, HIV, severe URTI, gastrointestinal disease, etc..., which may interfere with the clear classification of the treatment outcome. A medical review of the experienced diseases will be performed to define the list of patients excluded from the EE population.
  5. No major protocol violation. The list of all protocol violations will be assessed with regards to their impact (major/minor) prior to database lock.
- The list of patients excluded from the EE population will be reviewed and approved prior to study unblinding and database lock.

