#### Primary Efficacy Endpoint

The primary efficacy endpoint for the study is the cure rate on Day 14.

Cure on Day 14 will be defined as no parasitemia on Day 14 irrespective of axillary temperature without previously meeting any of the criteria of treatment failure throughout the follow-up period.

Treatment failure is defined as any of the following:

- ◆ Clinical deterioration due to *P. vivax* illness requiring hospitalization in presence of parasitemia.
- ◆ Presence of parasitemia and axillary temperature  $\geq 37.5^{\circ}\text{C}$  any time between Day 3 and Day 28.
- ◆ Presence of parasitemia on any day between Day 7 and Day 28 irrespective of clinical condition.

Patients presenting a *P. falciparum* infection after clearance of *P. vivax* parasites should be treated accordingly and withdrawn. They should not be considered as *P. vivax* treatment failures.

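### The Day 3 site note contradicts the treatment-failure definition and the rescue rule for a patient who is febrile and parasitaemic on Day 3

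*Protocol*

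**What the plan says.** **The Day 3 note (Section 6, Assessment D3).** The first sentence reads: "If parasites and fever have not cleared on Day 3, the patient should be followed up until total clearance of parasites". The second reads: "If parasitaemia remains significant, the patient should be viewed as a treatment failure and withdrawn from the study". The note then asks for the Day 28 assessments before discharge and before rescue medication. It gives no parasite density, time point or temperature for the second sentence.

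**The failure definition (Definitions; Section 9.5.1, Primary Efficacy Endpoint; Attachment 3).** There are three routes:

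1. Clinical deterioration from *P. vivax* requiring hospitalisation, with parasitaemia.
2. Parasitaemia with axillary temperature of 37.5 °C or more, "any time between Day 3 and Day 28".
3. "Presence of parasitemia on any day between Day 7 and Day 28 irrespective of clinical condition".

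**The rescue rule (Section 4.11).** "Treatment failures will be treated with the best antimalarial therapy available in the country where the study is conducted".

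**The analysis set (Section 9.2).** The first EE criterion is "Having completed a full course of study medication and having known efficacy endpoints". The primary non-inferiority analysis of Day 14 cure is run on EE (Section 9.5.2).

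**Fever clearance (Definitions).** Fever counts as cleared only after "at least two consecutive normal body temperature measurements obtained within an interval of 8 to 24 hours, post-dosing".

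**The concern.** The note and the definition address the same patient and give different answers. Under Section 9.5.1, a patient with any parasitaemia and a temperature of 37.5 °C or more on Day 3 has failed, and Section 4.11 calls for rescue. Under the note, that patient is followed until parasites clear and becomes a failure only if parasitaemia stays significant, which each site must interpret for itself. Rescue could come at different times at different sites for the same clinical picture.

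There is also a possible scoring effect. The note lets a site declare failure, withdraw and rescue on parasitaemia alone, while Section 9.5.1 needs fever with it until Day 7. A patient rescued in between, without fever at any positive film, would carry a failure label from Section 6 but satisfy no criterion in Section 9.5.1, and would have no untreated Day 14 film. If such a patient were judged to lack a known endpoint, the primary analysis could lose someone because treatment failed.

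**Working it through.** **Step 1. Classify the patient under each text.**

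| Patient, Days 3 to 6, not hospitalised for deterioration | Section 6 note | Sections 9.5.1 and 4.11 |
|---|---|---|
| Parasitaemic, 37.5 °C or more | Follow to clearance; failure only if parasitaemia stays significant | Failure now; rescue |
| Parasitaemic, below 37.5 °C, fever not yet formally cleared | Failure and rescue if parasitaemia stays significant | Not a failure before Day 7 |

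Row 1 is a direct conflict of instruction. Scoring there is clear: criterion 2 is met. If Day 3 itself were read as outside the window, the same conflict would appear on Day 4 while the patient is being followed.

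Row 2 is the scoring gap. The note's second sentence most naturally refers to the patient in its first, whose parasites and fever have both not cleared. Because clearance needs two consecutive normal readings 8 to 24 hours apart, fever can be formally uncleared while the temperature is below 37.5 °C at each positive film from Day 3. If the site rescues before Day 7, criterion 2 fails for want of fever and criterion 3 fails on timing. No text says whether the note's failure label is a known endpoint for EE.

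**Step 2. Reproduce the planned size (Section 9.4).** Inputs: 90% cure in both arms, margin 10 points, two-sided 95% interval, 90% power. With the null-restricted variance, the rates are 0.9313 and 0.8313, so v0 = 0.2042, and v1 = 2 × 0.9 × 0.1 = 0.18:

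n = (1.96 × √0.2042 + 1.2816 × √0.18)² / 0.10² = 204.3, so 205 per arm. Then 410 / 0.90 = 455.6, so 456.

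Both match the protocol and neither is affected by this point.

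**Step 3. Effect of dropping a failure.** The protocol gives no frequency for row 2, so the counts below are assumptions. With PA the pyronaridine artesunate arm and CQ chloroquine, lower limit = (pPA − pCQ) − 1.96 × √[pPA(1 − pPA)/nPA + pCQ(1 − pCQ)/nCQ]. The base is 185/205 cured per arm (90.2%, close to the planned 90%).

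| Case | PA | CQ | Difference (points) | Lower limit (points) |
|---|---|---|---|---|
| Base | 185/205 | 185/205 | 0.00 | -5.74 |
| One CQ failure dropped | 185/205 | 185/204 | -0.44 | -6.13 |
| One PA failure dropped | 185/204 | 185/205 | +0.44 | -5.25 |

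For the base, the standard error is √(2 × 0.9024 × 0.0976 / 205) = 2.93 points, and 1.96 × 2.93 = 5.74. Non-inferiority is shown in all three rows.

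**Step 4. The same shift near the margin.** These examples are placed there on purpose.

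| PA | CQ | Lower limit (points) | Non-inferiority |
|---|---|---|---|
| 177/205 | 185/205 | -10.12 | not shown |
| 177/204 (one PA failure dropped) | 185/205 | -9.65 | shown |
| 178/205 | 185/205 | -9.57 | shown |
| 178/205 | 185/204 (one CQ failure dropped) | -9.97 | shown |
| 178/205 | 185/203 (two CQ failures dropped) | -10.36 | not shown |

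One patient moves the limit by about 0.4 to 0.5 points, in either direction depending on the arm.

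**The case against.** On the site instruction, the other side can say that the note follows the bullet on discharging patients who are free of parasites and fever, so it may only mean whom to keep under observation, and it does not forbid rescue of someone already meeting the definition. That softens the conflict but does not remove it: the note goes on to state its own condition for failure and withdrawal, and that condition differs from Section 9.5.1.

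On the scoring gap, the objections carry real weight:

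- Day 3 temperatures and films are taken every 8 hours. A patient with one normal reading is measured again about 8 hours later. A second normal reading clears the fever; a reading of 37.5 °C or more with parasites present meets criterion 2. The window is normally about one measurement interval.
- The Definitions and Attachment 3 introduce the failure list with the word includes; only Section 9.5.1 presents it as a closed list. The note itself calls the patient a failure, so a known endpoint is a plausible reading.
- EE exclusions are approved before unblinding, the analysis is repeated in the intent-to-treat population, and a statistical analysis plan not seen here may settle the scoring.

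Two stronger readings are tempting. A reader might infer that the protocol excludes these patients from EE. It does not say so. The EE rule on interfering medication adds little: it is subject to medical review, and Section 3.3 does not class antimalarials given for treatment failure as a violation. A reader might also infer that every afebrile, parasitaemic patient on Days 3 to 6 is exposed, and that several such patients in the PA arm could decide the trial. The note applies where fever as well as parasites has not cleared, no document supports such numbers, and the Introduction says artemisinins clear parasites within 48 hours in most cases.

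**Conclusion.** The contradiction in site instructions holds. A febrile, parasitaemic patient on Day 3 is a failure due rescue under Sections 9.5.1 and 4.11, and a patient to be followed under Section 6 unless an undefined condition is met. This affects care and the timing of rescue. It does not affect how that patient is scored.

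The scoring gap is a secondary risk, not a stated rule. It needs a patient whose fever is formally uncleared, who is below 37.5 °C at every positive film, is rescued before Day 7, is not hospitalised for deterioration, and is then judged to have no known endpoint. This is probably rare. On the clearance statement in the Introduction, such patients are more likely in the chloroquine arm, where losing them makes non-inferiority harder to show; losing them from the PA arm would make it easier. At the planned cure rate the conclusion does not change, and it changes only in examples set at the margin. The point is minor.

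**What to change.** 1. **Section 6, Day 3 note.** Reword it so that parasitaemia with axillary temperature of 37.5 °C or more from Day 3 is a treatment failure to be rescued under Section 4.11. Patients with parasitaemia below 37.5 °C are followed, and failure is declared under the criteria in Section 9.5.1. Delete the sentence that turns on significant parasitaemia. No new density criterion before Day 7 is needed; adding one would alter a list that Attachment 3 attributes to a WHO report.

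2. **Sections 9.2 and 9.5.1.** Add one sentence: a patient who completed the full course and is withdrawn or rescued for persistent or recurrent *P. vivax* parasitaemia before a cure time point counts as a failure at that and later time points, and is not excluded from EE for the rescue or the missing later films. Patients rescued after withdrawal for vomiting stay under the existing EE criteria, including "No missed dose due to vomiting".

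The cost is wording only, with no new data and no extra patients. The observed cure rate may be slightly lower, because some patients who might have been dropped will count as failures. Sites lose the option of declaring failure on parasite density alone before Day 7 in an afebrile patient, but withdrawal for safety reasons under Section 3.3 and the hospitalisation criterion remain.

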## 7. STUDY ADMINISTRATION

### 7.1. Monitoring

Study monitors will contact and visit the Investigator regularly and will be allowed, on request, to inspect the various records of the study provided that patient confidentiality is maintained in accord with local requirements.

Before the initiation of the study, a representative of the Sponsor will visit the investigational site to:

- Determine the adequacy of the facilities in the context of malaria endemic countries
- Discuss with the Investigator(s) (and other personnel involved with the study) their responsibilities with regard to protocol adherence, and the responsibilities of Sponsor or its representatives

During the study, the monitor or another representative of the Sponsor will have regular contacts with the investigational site, including visits to:

- Provide information and support to the Investigator(s)
- Confirm that facilities and equipment remain acceptable
- Confirm that the investigational team is adhering to the protocol, that data are being accurately recorded in the CRFs, and that investigational product accountability checks are being performed
- Perform source data verification (a comparison of the data in the CRFs with the source records relevant to the study). This will require direct access to all original records for each patient (e.g. clinic charts, laboratory test reports) where relevant. A description of source data will be described in the monitoring plan.

The monitor or another representative of the Sponsor will be available between visits if the Investigator(s) or other staff at the centre needs information and advice.

The Investigator shall agree to co-operate with the study monitor to ensure that any problems detected in the course of these monitoring visits are resolved in a timely manner.

## **7.2. Special Consideration of Safety Monitoring**

### **7.2.1. Medical monitor responsibilities**

The Study Medical Monitor will be responsible for the evaluation of safety aspects of the study. This includes the review of available information from the regional medical monitors and the weekly status. Furthermore, the medical monitor would review and assess all reports of SAEs and determine whether these events must be reported to the competent authorities.

### **7.2.2. Sponsor responsibilities**

Sponsors' representatives will promptly notify all concerned Investigators, IEC and the regulatory authorities of findings that could adversely affect the safety of patients, impact the conduct of the study, or alter the IEC's approval/favourable opinion to continue the study. In addition, Sponsors' representatives will expedite the reporting to all concerned Investigators/institutions, to the IEC and to the regulatory authorities of all adverse drug reactions that are both **serious and unexpected**.

## **7.3. Audits and Inspections**

Authorised representatives of Sponsor, a regulatory authority, an IEC or an IRB may visit the centre to perform audits or inspections, including source data verification. The purpose of a Sponsor audit or inspection is to systematically and independently examine all study-related activities and documents to determine whether these activities were conducted, and whether data were recorded, analysed and accurately reported according to the protocol, Good Clinical Practice (GCP), guidelines of the International Conference on Harmonisation (ICH), and any applicable local regulatory requirements. The Investigator should contact Sponsor immediately if they are contacted by a regulatory agency about an inspection at their centre.

## **7.4. Training of Staff**

The principal Investigator will maintain a record of all individuals involved in the study (medical, nursing and other staff). He or she will ensure that appropriate training relevant to the study is given to all these staff, and that they will receive any new information of relevance to the performance of this study.

### **7.5 Changes to the Protocol**

Study procedures will not be changed without the mutual agreement of the Investigator(s) and Sponsors.

If it is necessary for the study protocol to be amended, the amendment or a new version of the study protocol must be notified to or approved by each IEC or IRB, and in many countries also the local regulatory authority, before implementation. Local requirements must be followed.

If a protocol amendment requires a change to a particular centre's Informed Consent Form, Sponsor and the centre's IEC or IRB must be notified. Approval of the revised Informed Consent Form by Sponsor and by the IEC or IRB is required before the revised form can be used.

Sponsor will distribute amendments and new versions of the protocol to each principal Investigator(s), who in turn is responsible for the distribution of these documents to his or her IEC or IRB, and to the staff at his or her centre. The distribution of these documents to the regulatory authority will be handled according to local practice.

### **7.6. Data Handling and Record Keeping**

CRFs will be provided for each patient. Patients will be identified by the patient identification number and the study identification number on all study documents.

All data on the CRF must be legibly recorded in black ink or typed. A correction should be made by drawing a single line through the incorrect entry and entering the correct information adjacent to it. The correction must be initialed and dated by the Investigator or a designated, qualified individual. Any requested information that is not obtained as specified in the protocol should have an explanation noted on the CRF as to why the required information was not obtained.

The Investigator must maintain adequate and accurate records to enable the conduct of the study to be fully documented and the study data to be subsequently verified. These documents should be classified into two separate categories:

- The Investigator's study file.
- The patient's clinical source documents.

The Investigator's study file will contain the protocol, amendments, CRF and query form, independent EC and regulatory approval together with the relevant correspondence, example of the patient informed consent form and patient information sheet, drug records, staff curricula vitae and authorization forms and other appropriate documents or correspondence.

Patient clinical source documents (usually defined by the project in advance to record key efficacy or safety parameters independent of the CRFs) would include patient hospital or clinic records, physician's and nurse's notes, appointment book, original laboratory reports, ECG, pathology and special assessment reports, signed informed consent forms, consultant letters, and patient screening and enrollment logs.

All study-related documents must be kept on file by the Investigator until at least 15 years after the last approval of a marketing application in an ICH region and until there are no pending or contemplated marketing applications in an ICH region or at least 15 years have elapsed since the formal discontinuation of clinical development of the investigational product. However, these documents should be maintained for a longer period if required by local applicable regulatory requirements. No documents should be destroyed without prior written agreement between the Sponsor and the Investigator. Should the Investigator wish to assign the documents to another party or move them to another location, the Sponsor must be notified in writing before the documents are reassigned or moved.

If the Investigator cannot guarantee the archiving requirement at the investigational center for any or all of the documents, special arrangements must be made between the Investigator and the Sponsor to store these in a sealed container(s) away from the center so that they can be returned sealed to the Investigator in case of a regulatory audit. Where source documents are required for the continued care of the patients, appropriate copies should be made prior to storing away from the center.

The Sponsor reserves the right to terminate the study at any time. Should this be necessary, both the Sponsor and the Investigator will arrange the procedures on an individual study basis after review and consultation. In terminating the study,

the Sponsor and the Investigator will assure that adequate consideration is given to the protection of the patient's interests.

#### **7.7. Patient Confidentiality**

The CRF as well as all reports and communications relating to patients in the study will identify each patient only by the patient's initials (first, middle, last) and by the patient identification number. The Investigator will maintain a current confidential Patient Identification Code List of names of all patients allocated to patient identification numbers in this study. This list will allow the Investigator to reveal the identity of the patients in the event that they need to be contacted for safety reasons. This information will be held in the strictest confidence and will only be used for emergency purposes, if needed.

All CRF pages are used to transmit the information collected in the performance of this study to the Sponsor and to governmental agencies, as appropriate. All pages of the CRF must be completed for each patient who receives any amount of study medication.

Portions of the patient's medical records pertinent to the study will be reviewed by the Sponsor personnel or their designee and possibly by regulatory authority personnel to assure adequate source documentation, accuracy, and completeness of the CRFs.

